### Intervention

Mechanical ventilation is performed during general anesthesia and intensive care unit (ICU) on volume-controlled mode. All patients are ventilated with low tidal volumes (6–8 mL/kg of predicted body weight) before and after CPB; ventilation is interrupted during CPB. The predicted body weight is calculated with the formula: 50 + 0.91*(Height in cm − 152.4) in men and 45.5 + 0.91*(height in cm − 152.4) in women. The respiratory rate will be adjusted before and after CPB by the anesthesiologist and/or intensivist to maintain end-tidal CO_2_ partial pressure between 35 and 45 mmHg. The lowest fraction of inspired oxygen (FiO_2_) will be targeted in both groups to maintain SpO_2_ ≥ 96%. The inspiratory to expiratory ratio (I:E) is set at 1:2. Positive end-expiratory pressure (PEEP) is set according to low PEEP/FiO_2_ table for ARDS [26] before and after CPB (Table 1). During sternal sawing, PEEP is temporarily set to 0 cmH_2_O to prevent pleural injury. No additional recruitment maneuvers are performed in both groups.

**Table 1 Tab1:** Low PEEP/FiO_2_ table

FiO_2_, %	30	40	40	50	50	60	70	70	70	80	90	90	90	100
PEEP, cmH_2_O	5	5	8	8	10	10	10	12	14	14	14	16	18	18–24

The intervention timeframe commences at randomization and concludes at endotracheal extubation, postoperative day 7, or death, whichever occurs first (i.e., during intraoperative and invasive mechanical ventilation in ICU). In the event of reintubation within postoperative day 7, patients will resume the intervention based on their assigned group.

#### Experimental strategy: intermittent sigh breaths plus lung protective ventilation

Sigh breaths are administered by elevating the positive end-expiratory pressure (PEEP), targeting a plateau pressure (Pplat) of 35 cmH_2_O (or 40 cmH_2_O for patients with a body mass index (BMI) > 35 kg/m^2^, considering chest wall compliance would be reduced in those patients). The appropriate delta level of PEEP necessary to achieve the target Pplat is determined manually prior to the initiation of sigh breaths. These sigh breaths will be administered over a 5-s interval once every 6 min, a methodology informed by the findings of Bendixen [27] and SiVent study [24]. Sigh breaths will be administered manually by an anesthesiologist in the operating room, while through ventilators configured to deliver sigh breaths in the ICU, utilizing equipment such as Mindray SV300 or Mindray SV600 or Mindray SV800 or Drager Evita Infinity V500, depending on availability.

Sigh breaths are administered at predetermined intervals throughout the entire duration of invasive mechanical ventilation:From endotracheal intubation to the surgical opening of the chest cavityFrom the surgical closure of the chest cavity to exiting the operating roomFrom ICU admission to the start of the spontaneous breathing trial

Patient needs not continue to receive sigh breaths during the time out of operating room and ICU (i.e., transported to CT, transported from operation department to ICU. Sigh breaths should be restarted on their return).

Subsequent sigh breaths will be suspended if the systolic arterial pressure drops below 90 mmHg, despite adequate administration of fluids and/or vasoactive drugs. Sigh breaths will resume once the systolic arterial pressure returns to ≥ 95 mmHg and remains stable for at least 5 min. Records of sigh interruption will be documented and analyzed (Table 2).

**Table 2 Tab2:** Perioperative ventilatory protocol in each of the two treatment arms

	**Experimental strategy**	**Control strategy**
From endotracheal intubation to chest cavity opening	LPV + sigh breaths	Lung protective ventilation (LPV) • Tidal volume 6–8 mL/kg PBW • PEEP: ARDS low PEEP-FiO_2_ table • RR ETCO_2_ 35–45 mmHg • FiO_2_ lowest to maintain SpO_2_ ≥ 96% • I:E ratio 1:2
Lung recruitment maneuvers	No	No
During chest cavity opening	Lung protective ventilation	Lung protective ventilation
During CPB	Ventilation interrupted	Ventilation interrupted
Ventilation after chest cavity closure (including in ICU)	LPV + sigh breaths	LPV

*LPV* lung protective ventilation, *ICU* intensive care unit, *CPB* cardiopulmonary bypass, *FiO*_*2*_ inspired oxygen fraction, *I:E* inspiratory time to expiratory time ratio, *PEEP* positive end-expiratory pressure, *PBW* predicted body weight, *RR* respiratory rate, *SpO*_*2*_ pulse oximetry, *ETCO*_*2*_ end-tidal CO_2_

#### Control strategy: lung protective ventilation

Patients are ventilated with low tidal volumes (6–8 mL/kg of predicted body weight) before and after CPB; ventilation is interrupted during CPB. PEEP is set according to low PEEP/FiO_2_ table for ARDS. Ventilation is interrupted during CPB (Table 2).

#### Rescue therapy

In both groups, unplanned recruitment maneuvers are permitted as rescue therapy in case of hypoxemia during the intervention period. Hypoxemia is determined as SpO_2_ ≤ 92% despite FiO_2_ of 80%.

### Standard of care

#### Surgery

The type of drugs used for the anesthesia, the management of the CPB, and fluid and transfusion strategies are implemented according to local protocol.

#### Extubation protocol

Patients will be excluded from the protocol if one of the following criteria is met:Postoperative continuous drainage exceeding 100 mL per hour for 3 consecutive hours.Left ventricular ejection fraction less than 30% or signs suggesting persistent deteriorating heart failure.Presence of escalating pericardial effusion or evident manifestations of obstructive shock.Perturbations in internal milieu: pH below 7.35 or above 7.45, serum potassium less than 3.0 mmol/L or greater than 5.5 mmol/L; blood lactate concentration ≥ 6 mmol/L.Hourly urine output less than 0.5 mL/kg/h.Difficulty in endotracheal intubation during anesthesia.Persistent hypothermia despite aggressive rewarming measures, with temperatures below 36 °C.Newly onset arrhythmias: heart rate below 40 beats/min or above 140 beats/min; ventricular rhythm disturbances; atrial fibrillation accompanied by hemodynamic instability.

After excluding the aforementioned conditions, the patient will enter a rapid extubation protocol. The tidal volume will remain unchanged, while adjusting the positive end-expiratory pressure (PEEP) to 5 cmH_2_O. Sedative medications will be discontinued, and analgesic medication dosages will be adjusted personally. During this period, close monitoring of the patient’s oxygenation, blood pressure, and other vital signs will be conducted. After 1–2 h, depending on the patient’s arousal status, readiness for a spontaneous breathing trial (SBT) will be assessed. Patients meeting the following criteria will undergo an SBT:Pulse oximetry saturation ≥ 92% given inspired oxygen fraction (FiO_2_) ≤ 40%.Alertness, able to follow commands, without agitation (Richmond Agitation-Sedation Scale [RASS] score of − 2 to 0).Hemodynamically stable (norepinephrine dose ≤ 0.1 µg/kg/min or equivalent doses of other vasopressor agents; or gradual tapering of vasopressor medications over the past 4 h).No potential short-term need for controlled ventilation due to other reasons.

During the 30-min spontaneous breathing trial (SBT) conducted in pressure support ventilation (PSV) mode with PEEP set at 5 cmH_2_O and PSV between 5 and 10 cmH_2_O, if any of the following conditions are met at the end of the 30-min period, the patient will fail the SBT:Respiratory rate > 35 breaths per minute or significant accessory muscle involvement.Oxygen saturation (SpO_2_) < 92%.Heart rate > 140 beats per minute or an increase in heart rate > 20%, or newly onset arrhythmias.Systolic blood pressure > 180 mmHg or < 90 mmHg.Patient reports significant respiratory distress.Evidence of active myocardial ischemia (dynamic ST-segment changes on electrocardiogram monitoring).Significant alteration in consciousness (Glasgow Coma Scale [GCS] score < 13, Richmond Agitation-Sedation Scale [RASS] score <  − 3), weak cough effort, or inadequate airway clearance capability.

Patients who fail the SBT will be reverted to controlled ventilation or pressure support ventilation mode as deemed appropriate. A subsequent SBT screening and assessment will be conducted if the symptoms listed above are effectively relieved, with ventilation continued according to the predefined group allocation.

#### Post-extubation ventilatory support

After extubation, routine oxygen therapy is typically administered via nasal cannula or face mask. For patients receiving face mask oxygen therapy at a flow rate of ≥ 5 L/min and failing to achieve a pulse oximetry level greater than 92% or respiratory rate ≤ 25 breaths/min will be considered for escalation to high-flow oxygen therapy (HFNO) or non-invasive ventilation (NIV), specific option depends on the clinical judgment of the attending physician, and no priorities will be predefined [28].

##### High-flow nasal oxygen (HFNO) therapy

Initial parameters for HFNO therapy include a flow rate of 30 L/min and an oxygen concentration of 100%. Subsequently, oxygen concentration will be titrated to maintain pulse oximetry within the range of 92–98%, and adjust the flow rate to the maximum tolerated by the patient, all maneuvers will completed within the first 10 min after HFNO therapy initiation. Subsequent adjustments in oxygen concentration and flow rate are made based on the target pulse oximetry (SpO_2_ 92–98%) and personal tolerance. If the patient meets the criteria of FiO_2_ less than 40% and respiratory rate < 25 breaths/min after high-flow therapy, an HFNO weaning trial will be conducted.

Maintaining the oxygen concentration and reduce the flow rate to 10 L/min, and maintain for 10 min. If the patient maintains a pulse oximetry between 92 and 98% and a respiratory rate of ≤ 25 breaths/min during the trial, HFNO can be discontinued, and conventional nasal cannula or face mask oxygen therapy can be initiated. If the patient does not pass the HFNO weaning trial, HFNO therapy will continue.

For patients who fail the HFNO weaning trial for the first time, if they subsequently meet the following criteria during HFNO therapy: FiO_2_ less than 40%, flow rate less than 30 L/min, and respiratory rate < 25 breaths/min, consideration may be given to discontinuing HFNO therapy and switching to regular nasal cannula or face mask oxygen therapy after passing the HFNO weaning trial. If oxygen saturation falls below 92% or respiratory rate exceeds 25 breaths/min during subsequent treatment, HFNO therapy can be resumed.

##### Non-invasive ventilation (NIV)

Initial parameters for NIV include an inspiratory positive airway pressure (IPAP) of 8 cmH_2_O, expiratory positive airway pressure (EPAP) of 5 cmH_2_O, and FiO_2_ of 100%. Subsequently, IPAP is adjusted within the range of 5–15 cmH_2_O to achieve a tidal volume of 6–8 mL/kg and a respiratory rate < 25 breaths/min. FiO_2_ is adjusted within the range of ≤ 60%, and EPAP within the range of 5–10 cmH_2_O to maintain SpO_2_ between 92 and 98%. Once oxygenation and respiratory distress symptoms improved, intermittent use of NIV will be considered, and NIV can be discontinued if applied for less than 4 h daily.

#### Reasons for reintubation

Reintubation indications include emergent anesthesia intubation for postoperative complications such as significant bleeding or cardiac tamponade requiring urgent reoperation, altered consciousness (Glasgow Coma Scale [GCS] score < 12), cardiac arrest or malignant arrhythmias, severe hemodynamic instability (norepinephrine dose > 0.1 µg/kg/min or equivalent doses of other vasopressor agents), and deteriorating respiratory failure (meeting at least two of the following criteria): unresolved hypoxemia (PaO_2_ < 60 mmHg or pulse oximetry persistently below 90% despite high-flow nasal oxygen [HFNO] at a flow rate exceeding 30 L/min and 100% oxygen concentration), respiratory acidosis (pH < 7.30, PaCO_2_ > 50 mmHg), respiratory rate > 30 breaths/min, inability to effectively clear airway secretions.

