The secondary endpoints include:Respiratory failure by post-extubation day 7No respiratory failure: SpO_2_ ≥ 90% after breathing ambient air for 10 min (excluding hypoventilation)Mild respiratory failure: SpO2 < 90% or PaO2 < 60 mmHg after breathing ambient air for 10 min (excluding hypoventilation) and corrected with 1–3 L/min with a nasal cannulaModerate respiratory failure: SpO2 < 90% or PaO2 < 60 mmHg despite a 3 L/min oxygen supply with a nasal cannula (excluding hypoventilation) and corrected with an oxygen supply from 4 to 10 L/min with a face maskSevere respiratory failure: SpO2 < 90% or PaO2 < 60 mmHg despite a 10 L/min oxygen supply with a face mask (excluding hypoventilation) and corrected with an oxygen supply > 10 L/min with a high-flow face mask or with non-invasive ventilation or with high-flow nasal oxygen therapy or with invasive mechanical ventilationSeverity of postoperative pulmonary complications by postoperative day 7, scored on an ordinal scale ranging from 0 to 5, using a modified definition of pulmonary complications [10]Grade 0: No symptoms or signalsGrade 1: One of the following: dry cough, abnormal lung findings and temperature 37.5 °C or higher with normal chest radiograph, or dyspnea without other documented causeGrade 2: Two of the following: productive cough, bronchospasm, hypoxemia (SpO2 90%) at room air, atelectasis with gross radiological confirmation (concordance of 2 independent experts) plus either temperature higher than 37.5 °C, or abnormal lung findings, hypercarbia (PaCO2 > 50 mmHg) requiring treatmentGrade 3: One of the following: pleural effusion resulting in thoracentesis, pneumonia, pneumothorax, extended noninvasive ventilation or high-flow nasal cannula, or reintubation lasting less than 48 hGrade 4: Reintubation or invasive mechanical ventilation for 48 h or moreGrade 5: Death before hospital dischargeInvasive mechanical ventilation (IMV) days in ICU by postoperative day 7Duration of invasive mechanical ventilation by postoperative day 7, initiated from ICUadmission.Use of high-flow nasal cannula or non-invasive ventilation by postoperative day 7.Use of new invasive mechanical ventilation by postoperative day 7.No ventilatory support days by postoperative day 7.No ventilatory support days are defined as days without invasive mechanical ventilation,high-flow nasal cannula, and non-invasive ventilation.In-hospital mortalityDeath occurred during hospital stay, time frame from the day of surgery up to hospitaldischarge or death, maximum censoring at day 28 after surgery.ICU length of stayDays since surgery until ICU discharge. The censoring will be performed at day 28 aftersurgery. Patients dying before leaving the ICU were censored as not discharged from ICU atday 28 after surgery.Length of hospital stayDays since surgery until hospital discharge. The censoring was performed at 28 days. Patientsdying before leaving the hospital were censored as not discharged from hospital at day 28.Adverse events by postoperative day 7:Use of high-dose vasopressors (> 1 µg/kg/min of norepinephrine)Postoperative barotraumaDefined as the presence of radiological evidence suggesting pneumothorax, mediastinal emphysema, new-onset pulmonary emphysema, or subcutaneous emphysema.Reoperation before the 12th postoperative hour

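### The tapering route into the spontaneous breathing trial overlaps with the norepinephrine indication for reintubation, and any resulting reintubation scores as a pulmonary complication whatever its cause

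*Protocol article*

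**What the plan says.** All references are to the protocol article.

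- **Extubation protocol.** One condition for entering the SBT is "Hemodynamically stable (norepinephrine dose ≤ 0.1 µg/kg/min or equivalent doses of other vasopressor agents"; the same condition continues "or gradual tapering of vasopressor medications over the past 4 h". The two parts are alternatives, and the second carries no dose.
- **Reasons for reintubation.** The list of indications includes an entry that opens "severe hemodynamic instability (norepinephrine dose" and sets the limit at more than 0.1 µg/kg/min, or the equivalent of another vasopressor. The requirement for two criteria belongs to another item in that list, "deteriorating respiratory failure (meeting at least two of the following criteria". The hemodynamic item therefore stands alone.
- **Study endpoints.** The PPC scale puts reintubation of under 48 h in grade 3, reintubation of 48 h or more in grade 4, and death before discharge in grade 5. None of these is limited by cause. A separate endpoint is "Use of new invasive mechanical ventilation by postoperative day 7", also without a restriction by cause.
- **Abstract and Statistical analysis.** PPC severity by postoperative day 7 is the main secondary endpoint. It is analysed by Mann–Whitney test and by ordinal logistic regression.

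**The concern.** One vasopressor state should not count as stable when the tube is to come out and as severely unstable once it is out. As printed, the two sections allow that, which is an inconsistency in safety wording.

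It also bears on what the main secondary endpoint measures. A patient with no lung problem could be reintubated on a vasopressor dose and move from a possible PPC grade 0 to grade 3 or 4. The same event would enter the new-ventilation endpoint. A difference between arms in such events would be read as pulmonary when its origin was circulatory.

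**Working it through.** No figure in the plan needs reproducing here. The check compares two printed rules and then follows the event into the endpoints.

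**Step 1. The rules as logical conditions.** Let d be the norepinephrine dose in µg/kg/min.

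- Hemodynamic condition for the SBT: d ≤ 0.1, or a gradual taper over the past 4 h.
- Hemodynamic indication for reintubation: d > 0.1.

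**Step 2. Illustrative doses.**

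| Dose | Tapering | Stable for SBT | Reintubation indication |
|---|---|---|---|
| 0.05 | no or yes | yes | no |
| 0.10 | no or yes | yes | no |
| 0.11 | no | no | yes |
| 0.11 | yes | **yes** | **yes** |
| 0.15 | no | no | yes |
| 0.15 | yes | **yes** | **yes** |
| 0.30 | no | no | yes |
| 0.30 | yes | **yes** | **yes** |

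The numeric limits alone are complementary and do not clash. The overlap comes entirely from the tapering route. That route admits additional patients only when d > 0.1, so everyone it adds is in the overlap at SBT entry.

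**Step 3. Does anything in between close the gap?** Two other lists apply before extubation.

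- The conditions that keep a patient out of the rapid extubation pathway include bleeding, failing ventricular function, obstructive shock, raised lactate and low urine output. They contain no vasopressor dose.
- The SBT failure list contains systolic pressure below 90 or above 180 mmHg, and also no vasopressor dose.

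A patient with acceptable pressure on a tapering dose above 0.1 can therefore pass both. The overlap ends only if the dose reaches 0.1 or below before the tube is removed.

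**Step 4. Where the event lands.** For a purely hemodynamic reintubation by postoperative day 7:

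- PPC grade 3 if it lasts under 48 h, grade 4 if 48 h or more, and grade 5 if the patient dies before discharge.
- It counts as new invasive ventilation.
- It does not by itself meet the respiratory-failure scale, because every failure grade there requires low SpO2 or PaO2.

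**Step 5. Size.** The protocol gives no rate of vasopressor use at extubation and no reintubation rate, so the number of patients cannot be computed. The weight of a single event can. With 96 patients planned per arm, one such reintubation changes that arm's proportion with new invasive ventilation by 1/96 = 0.0104, about 1.0 percentage point.

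**The case against.** The strongest reply is that the overlap is a matter of wording and will rarely matter in practice. Much of this stands.

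- The tapering clause governs entry to the SBT, not extubation. A patient must clear the other exclusions, pass a 30-minute trial and still be above 0.1 afterwards.
- Another SBT condition rules out patients who may soon need controlled ventilation for other reasons. This could be read to cover the overlap, but it names no dose and is only a partial safeguard.
- The reintubation section lists indications and does not make reintubation mandatory at that dose. A clinician may well not reintubate a patient who has just passed the SBT and is being weaned. A reader might infer that everyone extubated by the tapering route becomes a PPC event; the documents do not support that.
- All-cause counting is defensible. The scale is described as a modified published definition, the Discussion values comparability with other studies, and counting every cause avoids disputes over attribution. Reintubation for bleeding, tamponade, arrest or reduced consciousness enters the score in the same way.

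Three further readings go beyond the text. The adverse event "Use of high-dose vasopressors (> 1 µg/kg/min of norepinephrine" might be taken as a third conflicting threshold, but it defines a safety outcome rather than a trigger for reintubation. The primary endpoint might be thought compromised, but it is SpO2/FiO2 over the first hour after extubation and does not score reintubation. Only a reintubation inside that hour could touch it, and nothing shows how often that would occur. Finally, a bias between arms might be inferred. The same rules apply to both arms, and the protocol gives no vasopressor data by arm, so such a bias is possible but not shown.

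None of this removes the overlap. Both rules are printed with their limits, so condensation of the article does not explain it.

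**Conclusion.** The inconsistency is real and limited. The two sections disagree for one group: patients whose vasopressors are being tapered, whose norepinephrine is still above 0.1 µg/kg/min, and who are extubated before it falls to 0.1 or below. If such a patient is reintubated for that indication, the main secondary endpoint and the new-ventilation endpoint record an event with no pulmonary cause.

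The number affected is unknown and probably small, and the consequence lies in secondary endpoints. The sample size and the planned primary comparison are not in question. The conclusion rests on reading the tapering clause as a true alternative and the hemodynamic indication as sufficient alone; the punctuation and wording of both sections support that reading. It is worth correcting because the remedy is cheap and serves both safety consistency and interpretation of the PPC score.

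**What to change.** 1. The clinical team should reconcile Extubation protocol and Reasons for reintubation so that the same vasopressor state cannot satisfy both. Which threshold or rule applies is for that team to decide.
2. Keep the all-cause PPC score as the main analysis.
3. Add a sensitivity analysis of PPC severity and of new invasive ventilation in which reintubations for the non-respiratory indications listed under Reasons for reintubation are separated from respiratory ones. Use the recorded indication for each reintubation. The article does not list every data field, so this may already be collected; if not, it should be taken from source records.

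The cost is a wording amendment with ethics approval and one extra analysis. Attributing cause needs some judgement, particularly when circulatory and respiratory failure coincide, so it should be done by someone blind to allocation. The article expects recruitment to end in October 2024. If it has ended, the wording change comes too late for these patients, but the sensitivity analysis remains feasible.

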## Standard procedures

### Screening and inclusions

Patients are screened for inclusion and exclusion criteria during the preoperative visit by anesthesiologist. Patients who meet all inclusion criteria and do not meet any exclusion criteria will be included in the study after providing written, signed informed consent.

